## 2. Materials and Methods

### 2.1. Study Design and Setting 

This is an open label RCT being performed at a single level I trauma center: St. Anthony Hospital in Lakewood, CO. This RCT was designed primarily to determine whether adjunctive dronabinol reduces opioid consumption compared to control. The study was designed with a stratified randomization by baseline marijuana use, which is intended to determine whether the treatment effect of dronabinol is greater in chronic marijuana users compared to recreational or non-marijuana users. This stratified randomization design was incorporated based on the gestalt that cannabis-based medication has a greater benefit for marijuana users.

There is a 48-hour screening/randomization window, a 48-hour treatment window, and a total participation period extending through the acute hospitalization. A description of the clinical trial is posted at ClinicalTrials.gov.

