### 2.3. Study Visits

The following procedures will be performed at screening, within 48 h of hospital admission: ensure patient meets inclusion and exclusion criteria; record 24-hour total morphine equivalents; record habitual marijuana usage; obtain informed consent via patient or proxy. 

Once patients are confirmed to meet all criteria and have signed an informed consent, they will be randomized 1:1 across the two study arms (dronabinol or control, Figure 1). The following procedures will be performed during randomization: randomize the patient using the Microsoft Excel blinded randomization schema; record pain using the patient self-reported pain numeric rating scale (NRS, 0–10 scale). 

The following procedures will be performed during the acute hospitalization, post-randomization: if randomized to the dronabinol arm, administer the first dose within the first scheduled dose window and within 12 h of randomization. Record all doses received, including date, time and dose; record all opioid and non-opioid systemic analgesics received, including route/dose/frequency; record all non-analgesic concomitant medications; record pain NRS scores at the following time points: once admitted in hospital bed, preoperatively in the OR prior to anesthesia, one hour post operatively; record all analgesic complications; record all documented drug use from patient self-report and urine drug screening results. Detailed information on the regularity of marijuana use will also be recorded. 

The following procedures will be performed at hospital discharge: record discharge pain NRS score; record discharge location; re-consent, if necessary. 

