### 2.4. Randomization and Blinding

Patients will be assigned to treatment by a randomization schedule developed and maintained by an independent statistician. The randomization allocation sequence was computer generated and is blinded, with allocation hidden until a patient has met all inclusion and exclusion criteria and provided informed consent. Randomization will occur in a 1:1 fashion in blocks of 2 and 4 and stratified by habitual marijuana user (yes/no). 

The assessor, participants, treatment team, and statisticians are unblinded. All assessments are standard and routinely collected by the assessors (ICU and general ward nursing staff), including pain NRS scores and analgesia administration. 

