### 2.6. Outcome Measures

Patients will be followed to hospital discharge for outcomes of morphine equivalent use, length of stay, pain NRS scores, hospital complications, and analgesic complications. 

The primary outcome is morphine equivalents. All opioids consumed will be converted to morphine equivalents, as shown in Figure 1 [11]. The clinical effects of treatment arm on morphine equivalents will be evaluated at 48 h after randomization. 

Secondary outcomes include the following:Morphine equivalents: overall (hospital admission through discharge or death)Non-opioid analgesics: overall doses received (admission through acute hospitalization discharge or death), and examined by non-opioid drugAcute hospitalization length of stayPain NRS scores: in ED prior to randomization, once admitted in hospital bed, preoperatively in the OR prior to anesthesia, one-hour post operatively, at hospital dischargeTime (hours) to transition to non-opioid analgesiaIncidence of hospital complicationsSafety (Incidence of analgesic complications)

Analgesic complications will be recorded irrespective of the presence or absence of a causal relationship, and include the including:Allergic reactionNausea and vomitingRespiratory depression (hypoxia and hypopnea)HypotensionUrinary retentionConstipation/ileusAbdominal painDizzinessEuphoriaParanoid reactionSomnolenceDeliriumOver-sedation.

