### 2.7. Statistics

Significance is set at an alpha value of 0.05. SAS (Cary, NC) software will be used for statistical analysis. All efficacy analyses will be performed in the intent-to-treat population, defined as all patients who are randomized. Subset analyses will be performed by habitual marijuana use. 

The primary endpoint is the change in morphine equivalents and will be assessed as: post-randomization (48 h after randomization) minus pre-randomization (24 h prior to randomization). No imputation will occur for the primary endpoint. The change in morphine equivalents (mg) will be analyzed with an analysis of covariance (ANCOVA) model to examine the effect of treatment arm, adjusted for age, gender, injury severity score, and clinical characteristics that differ between groups with *p* < 0.15. Of note, our study inclusion criteria allow for patients to present with polytrauma. We anticipate the majority of patients will have injuries to the thorax and extremities, with few patients presenting with severe TBI because administration of opioids and other drugs that alter a neurological assessment tend to be used sparingly. Should there be differences in injury patterns, despite the 1:1 randomization procedure, these differences will be adjusted for in the primary ANCOVA analysis.

Secondary efficacy analyses include the difference between treatment groups in: hospital disposition, hospital complications, and analgesic complications, reported as proportion (%) and analyzed with chi-square tests; morphine equivalents over the hospitalization, hospital length of stay (days), time (h) to transition to non-opioid analgesia, pain NRS scores at all specified time points, reported as median (IQR) and analyzed with a Wilcoxon rank-sum test. Analgesic complications will be described by severity as mild, moderate and severe.

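### None of the five listed pain scores is anchored to the 48 hours over which opioid use is measured, and one taken before randomization is tested as an efficacy outcome

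*Protocol article*

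**What the plan says.** **Pain outcomes.** Section 2.6 (Outcome Measures) lists pain NRS as a secondary outcome at five points. The first two are "in ED prior to randomization, once admitted in hospital bed". The others are in the operating room before anesthesia, one hour after surgery, and at discharge. Section 2.7 (Statistics) places "pain NRS scores at all specified time points" among the secondary efficacy analyses and compares the arms by Wilcoxon rank-sum test.

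**Collection.** Section 2.3 (Study Visits) has staff "record pain using the patient self-reported pain numeric rating scale (NRS, 0–10 scale") at randomization. Under the procedures that follow randomization it then says "record pain NRS scores at the following time points: once admitted in hospital bed", with the two operative scores after that and the discharge score in a separate paragraph.

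**Windows.** Section 2.1 states: "There is a 48-hour screening/randomization window, a 48-hour treatment window". Section 2.3 sets screening "within 48 h of hospital admission: ensure patient meets inclusion and exclusion criteria; record 24-hour total morphine equivalents". Section 2.7 defines the primary endpoint as "post-randomization (48 h after randomization) minus pre-randomization (24 h prior to randomization").

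**Conduct.** Section 2.4 leaves assessors, participants, treating team and statisticians unblinded, and adds: "All assessments are standard and routinely collected by the assessors", pain scores included. Section 2.5 (Intervention) gives as-needed analgesia in both arms against an NRS target of 4 or less. It states that this keeps analgesia independent of arm.

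**The concern.** A fall in opioid use is good news for an analgesic adjunct only if patients hurt no more while the opioids were reduced. That matters most where the people giving as-needed opioids know the assignment, because they may give less to patients whom they know to be on dronabinol. The natural check is a pain comparison over the period in which the opioids are counted. The listed pain outcomes follow the patient's route through the hospital (ED, bed, surgery, discharge) and not the time since randomization, so they need not fall in that period.

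A second problem is that a score taken before randomization sits among the efficacy comparisons. Treatment cannot affect it, so any difference there is chance, although it would be reported as an efficacy finding.

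**Working it through.** The plan gives no figure for pain, so there is none to reproduce. The check sets each listed score against the 0 to 48 h window of the primary endpoint.

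| Score (section 2.6) | Relation to 0–48 h after randomization | Basis |
|---|---|---|
| ED | Before it, by its own wording | 2.6 |
| Hospital bed | Unclear | 2.3 lists it after randomization, but randomization may come up to 48 h after admission |
| Preoperative | Surgical patients only; surgery is not tied to the window | 2.3, 2.6 |
| One hour postoperative | Same | 2.3, 2.6 |
| Discharge | No fixed time; may fall inside or after the window | 2.3, 2.5 |

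Scores anchored to the window: 0 of 5. Scores certain to precede randomization: 1 of 5.

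**The bed score.** Eligibility needs at least 50 mg of morphine equivalents within a 24-hour window (section 2.2), and the baseline is the 24 h before randomization (section 2.7). A patient randomized late in the screening period would be expected to be in a bed already, so the placement in section 2.3 cannot safely be read as true of everyone. A patient who reaches the threshold early could be randomized first. Even then, the first dronabinol dose may come up to 12 h after randomization (section 2.5), so the bed score may still precede treatment.

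**The baseline score.** Section 2.3 names five scores: randomization, bed, preoperative, postoperative and discharge. Section 2.6 names five: ED, bed, preoperative, postoperative and discharge. Four match. The fifth may be one measurement described in two ways, or two different measurements. The text does not settle it.

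**The test of the ED score.** At the alpha of 0.05 in section 2.7, a comparison that treatment cannot affect reaches significance about 5% of the time.

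**What a windowed score could detect (illustration).** The inputs are 122 / 2 = 61 per arm (section 2.8), two-sided alpha 0.05 and 80% power. The NRS standard deviation is not in the documents; I assume 2 to 3 points. The fraction operated on within the window is not given either; I assume one half.

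Detectable difference = (1.960 + 0.842) × SD × √(2/m), with m patients per arm.

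- Everyone scored, m = 61: 2.802 × 2 × √(2/61) = 1.01 points; with SD 3, 1.52 points.
- Half scored, m = 30.5: 1.43 points; with SD 3, 2.15 points.

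Under these assumptions, a score available in everyone detects about 1.0 to 1.5 points. One available only in surgical patients detects about 1.4 to 2.2 points, in a subgroup whose surgery may itself follow randomization.

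**The case against.** The strongest reply has three parts.

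**Safeguards exist.** Section 2.5 ties analgesia in both arms to self-reported pain, and section 2.4 says that ward and ICU nurses chart pain routinely. A reader might infer from the schedule that an opioid reduction could not be told from under-treatment at all. The documents do not support that: the target rule works against under-treatment, and charted scores could be used. What remains is that the rule is asserted and not measured. Scores of 5 or more only typically lead to analgesia, on clinical judgment, and no listed outcome checks whether the rule held equally in both arms.

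**Several scores may fall in the window.** A reader might also infer that the bed score normally precedes randomization, that discharge always follows the treatment period, or that the score at randomization was left out of the outcomes. None of these is established. Section 2.3 lists the bed score after randomization, and the documents give no distribution of time to randomization. No minimum stay is stated. The randomization score may be the one that section 2.6 calls the ED score. These are ambiguities to resolve.

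**An article condenses a fuller plan.** The choice of summary measure and model can reasonably be left to an analysis plan. But the article does state explicit time points and sends all of them to an efficacy test. The point concerns what is fixed, not what is left out.

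**Conclusion.** The point holds in this form: none of the five pain outcomes is anchored to the 48 h of the primary opioid endpoint, and at least one score that treatment cannot affect is tested as efficacy. As specified, the outcomes therefore do not check whether pain control was equal while opioid use was being compared.

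The primary analysis itself is untouched, and the false-positive risk on the ED score is about 5% on one secondary comparison. The weight lies in interpretation: a positive primary result would come without a prespecified pain comparison from the same period. If charted scores were picked later by statisticians who know the allocation, that comparison would be post hoc.

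The count of 0 of 5 rests on the text alone. Any statement about how often the bed, operative or discharge scores fall inside the window would need data that the documents do not give. The detectable differences rest on the assumed SD and surgical fraction.

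**What to change.** 1. Add a named secondary outcome that summarises routinely charted NRS from randomization to 48 h, for example a time-weighted mean. Compare the arms with adjustment for pre-randomization NRS and the randomization stratum (habitual marijuana use), and report the difference with a 95% CI beside the primary result.
2. Remove scores taken before randomization from the efficacy tests and use them only as baseline.
3. Reconcile sections 2.3 and 2.6: say whether the bed score is before or after randomization, and whether the ED and randomization scores are one measurement.

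The cost is extra data extraction and entry; by section 2.4 the scores are already collected. There are limits. The summary depends on ward charting frequency, which is not stated, and charting may be denser when pain is high. As-needed dosing to a target pulls NRS toward that target in both arms. Self-reported pain in an open-label trial also remains open to expectation bias. The new outcome would support the opioid result without being conclusive.

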### 2.7. Statistics

Significance is set at an alpha value of 0.05. SAS (Cary, NC) software will be used for statistical analysis. All efficacy analyses will be performed in the intent-to-treat population, defined as all patients who are randomized. Subset analyses will be performed by habitual marijuana use. 

The primary endpoint is the change in morphine equivalents and will be assessed as: post-randomization (48 h after randomization) minus pre-randomization (24 h prior to randomization). No imputation will occur for the primary endpoint. The change in morphine equivalents (mg) will be analyzed with an analysis of covariance (ANCOVA) model to examine the effect of treatment arm, adjusted for age, gender, injury severity score, and clinical characteristics that differ between groups with *p* < 0.15. Of note, our study inclusion criteria allow for patients to present with polytrauma. We anticipate the majority of patients will have injuries to the thorax and extremities, with few patients presenting with severe TBI because administration of opioids and other drugs that alter a neurological assessment tend to be used sparingly. Should there be differences in injury patterns, despite the 1:1 randomization procedure, these differences will be adjusted for in the primary ANCOVA analysis.

Secondary efficacy analyses include the difference between treatment groups in: hospital disposition, hospital complications, and analgesic complications, reported as proportion (%) and analyzed with chi-square tests; morphine equivalents over the hospitalization, hospital length of stay (days), time (h) to transition to non-opioid analgesia, pain NRS scores at all specified time points, reported as median (IQR) and analyzed with a Wilcoxon rank-sum test. Analgesic complications will be described by severity as mild, moderate and severe.

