### 2.8. Sample Size

The planned enrollment is 122 patients total randomized 1:1 across two study arms: dronabinol or no dronabinol (systemic analgesia only). The sample size is based on a 38% reduction in morphine equivalents with adjunctive dronabinol vs. an 8% reduction in morphine equivalents for systemic analgesics only, with a pooled standard deviation of 58. The analysis was performed using two sample mean tests with normal approximation and equal weights. These estimates were derived via bootstrapping of the final matched study sample of 66 patients. The power to demonstrate the main effect of dronabinol over systemic analgesics is 80% using a 2-tailed alpha of 0.05. 

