## 3. Discussion

This is the first randomized trial to investigate whether the addition of dronabinol is effective at reducing opioid consumption for acute pain management of traumatic injury. There are numerous strengths of this study. This clinical trial improves upon our previously published matched cohort study and removes many of the limitations of that study: patients will now be matched by self-reported marijuana use; the pre-treatment period for the controls will be identical to cases rather than being estimated based on the median time from admission to first administration of dronabinol among cases; we will know why controls were not prescribed dronabinol; there are complications and adverse effects that are associated with both systemic analgesics and dronabinol, which will be recorded and analyzed in this trial by treatment arm and by severity. Additional strengths of this study are that it is investigator-initiated and independent from pharmaceutical or other industry interests, and the findings (whether positive or negative) will be submitted to a peer reviewed scientific journal for publication.

Another benefit of this study is the stratified randomization by chronic marijuana usage. Earlier work by the study investigators suggests that pre-injury marijuana use results in increased consumption of opioid analgesics and greater self-reported pain following traumatic injury compared to trauma patients who are marijuana naïve [12]. If the randomized trial demonstrates a greater treatment effect in the subset of chronic marijuana users, this will have wide-ranging clinical implications for acute pain management, because trauma patients have a high prevalence of marijuana use and other substance abuse issues, reported in 40–50% of patients [13,14] that appears to be increasing over time [15]. Thus, if marijuana use significantly affects acute pain management then chronic marijuana users will merit special consideration during acute pain management. 

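### The stratification is meant to show whether dronabinol works better in chronic marijuana users, but the only analysis named for that is subset analyses, with no contrast between strata

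*Protocol article*

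**What the plan says.** Section 2.1 (Study Design and Setting) gives the purpose of stratifying by baseline marijuana use: it is "intended to determine whether the treatment effect of dronabinol is greater in chronic marijuana users compared to recreational or non-marijuana users". Section 2.4 sets the stratification factor as habitual marijuana use, yes or no.

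Section 2.7 (Statistics) gives this question one sentence: "Subset analyses will be performed by habitual marijuana use". The primary model in the same section is an ANCOVA of the change in morphine equivalents. It has treatment arm, age, gender, injury severity score and any clinical characteristic that differs between arms at p < 0.15. Neither habitual use nor its interaction with arm is named.

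Section 2.8 (Sample Size) states power for the overall comparison only: "The power to demonstrate the main effect of dronabinol over systemic analgesics is 80" per cent. The Discussion attaches broad consequences for pain management to one particular result: "If the randomized trial demonstrates a greater treatment effect in the subset of chronic marijuana users".

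**The concern.** Whether an effect is greater in one stratum than in another is a question about effect modification. The quantity that answers it is the difference between the two stratum-specific treatment effects, with its standard error, which is the treatment-by-stratum interaction. Stratified randomization balances the arms within strata but does not supply that comparison. An analysis within each subset estimates each effect without testing whether the two differ.

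The gap matters because of how subset results are commonly read. If one subset reaches p < 0.05 and the other does not, the pair is easily taken as evidence that the effect differs, and nothing controls the error rate of that reading. At stake is a conclusion that habitual users need separate treatment in acute pain management, drawn from data that could arise easily under one common effect.

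**Working it through.** **Inputs from section 2.8.** The effect is a "38% reduction in morphine equivalents with adjunctive dronabinol vs. an 8% reduction in morphine equivalents for systemic analgesics only", so 38 − 8 = 30 percentage points. The spread is stated "with a pooled standard deviation of 58", without a unit. There are 122 patients, 1:1, so 61 per arm. The power statement "is 80% using a 2-tailed alpha of 0.05" fixes the two-sided 5% level.

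**Assumed.** The SD is in the same units as the effect. The share f of habitual users is not stated; the Discussion's 40–50% covers marijuana use together with other substance abuse. I use f from 20% to 50%.

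**The plan's own figure first.** n per arm = 2 × (1.960 + 0.842)² × 58² / 30² = 58.7, so 59 per arm and 118 in total; the t-test version gives 60 per arm and 120. With 61 per arm, SE = 58 × √(2/61) = 10.5, z = 30/10.5 = 2.86, and power is 81.5% (80.9% by t-test) against the stated 80%. This is close to the planned 122 and supports reading the SD in percentage points.

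**Subset tests when the true effect is 30 points in both strata.** Users have 61f patients per arm and non-users 61(1 − f). In each stratum, SE = 58 × √(2/n) and power = Φ(30/SE − 1.96). With power p_u in users and p_n in non-users:

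- P(exactly one significant) = p_u(1 − p_n) + p_n(1 − p_u)
- P(users only) = p_u(1 − p_n)

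For f = 50%, n = 30.5 per arm, SE = 14.85, z = 2.02 and power is 52.4% in each stratum, so P(exactly one) = 2 × 0.524 × 0.476 = 0.499. For f = 20%, p_u = 24.7% and p_n = 72.4%, so P(users only) = 0.247 × 0.276 = 0.068 and P(non-users only) = 0.724 × 0.753 = 0.545.

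**Interaction test.** SE_int = 58 × √(2/n_u + 2/n_n). The difference detectable with 80% power is 2.80 × SE_int.

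| Habitual users | Power, users / non-users | Exactly one significant | Users only | Non-users only | SE_int | Interaction power, 30-point difference | Detectable at 80% |
|---|---|---|---|---|---|---|---|
| 50% | 52.4% / 52.4% | 49.9% | 24.9% | 24.9% | 21.0 | 29.8% | 58.8 |
| 40% | 43.9% / 60.0% | 51.2% | 17.6% | 33.6% | 21.4 | 28.8% | 60.1 |
| 30% | 34.6% / 66.6% | 55.1% | 11.6% | 43.6% | 22.9 | 25.8% | 64.2 |
| 20% | 24.7% / 72.4% | 61.3% | 6.8% | 54.5% | 26.3 | 20.8% | 73.6 |

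**Simulation.** In 40,000 simulated trials at each of 20%, 40%, 45% and 50% users, with the same effect in both strata, exactly one subset was significant in 49.9% to 61.3%. The interaction test rejected in 4.8% to 5.0%.

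**Two reference points.** With no effect in either stratum, exactly one subset is significant in 2 × 0.05 × 0.95 = 9.5% of trials. For 80% power on a 30-point interaction, N = 122 × (detectable/30)², which is about 470 patients at 50% users and about 730 at 20%.

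**The case against.** The strongest reply is that the article condenses a fuller protocol and an analysis plan that are not shown. The sentence in section 2.7 does not say that separate models will be fitted or within-stratum p-values compared, and it does not exclude an interaction term. This stands as far as it goes. One cannot conclude that the trial will have no interaction test, only that this document states an aim and names for it an analysis without the needed contrast. Two stratum estimates could be contrasted directly, but that contrast is the interaction test.

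Four stronger readings are tempting and not supported.

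- A reader might infer that the investigators will declare a differential effect because one subset is significant and the other is not. The document never says so. The Discussion speaks of a greater effect, not of which p-value crosses 0.05.
- A reader might take 50–61% as the chance of the particular false claim the Discussion would make. It counts splits in both directions. Only the users-only split fits that claim, and its chance is 7–25%. For comparison, a two-sided 5% interaction test errs in that direction about 2.5% of the time.
- A reader might see the preliminary study in the Introduction as a false split that has already happened. It is not one. A matched result is given for users (p = 0.01) but none for non-users. The p = 0.41 compares users with non-users among dronabinol recipients only, so it is not an interaction test. The authors themselves treat that evidence as inconclusive.
- A reader might quote about 59 points as the detectable interaction. That holds only near an even split, and on the percent scale of section 2.8, whereas the ANCOVA in section 2.7 models change in mg.

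It is also fair to say that the main arm comparison is clearly the primary objective. That lowers the weight of the point but leaves the purpose stated in section 2.1 unhedged.

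**Conclusion.** The point holds in a limited form. The article says the stratification is there to settle whether the effect is greater in chronic users, and names only subset analyses to do so. This is more than omitted detail: the aim is explicit, the analysis named for it lacks the contrast, and a better method on the existing stratification factor costs one model.

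If subset results are read by significance, a common 30-point effect would leave exactly one subset significant in about 50–61% of trials, and users only in about 7–25%. An interaction test would give a false positive in about 5%. These figures rest on SD 58 in percentage points, 61 per arm, unadjusted two-sample tests and an assumed 20–50% share of habitual users.

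The interaction test would not make 122 patients enough. Its power for a 30-point difference in effect is about 21–30%, and 80% power is reached only at about 59–74 points, roughly 2 to 2.5 times the effect the trial is sized for. The aim is therefore exploratory whatever model is used. The primary analysis is unaffected.

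**What to change.** In section 2.7, replace the subset sentence by a separate secondary model: the ANCOVA of the primary endpoint with habitual use (the stratification factor) and an arm-by-habitual-use interaction added. Report the interaction estimate with its 95% confidence interval and the stratum-specific effects from that same model. State that any claim of a greater effect in users rests on the interaction and not on within-stratum p-values.

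In section 2.1 and the Discussion, call this aim exploratory and say that power for it is low. Give the range: about 21–30% power for a 30-point difference, and 80% power only at about 59–74 points, on the percent scale of section 2.8 and depending on the unstated share of habitual users. Do not insert a single figure of 59 points.

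If the full protocol or analysis plan already specifies the interaction, aligning the article's wording with it is enough.

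The cost is one extra model and a more modest statement of the secondary aim. Enrolment, randomization, data collection and the primary analysis do not change.

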## Abstract

Delta-9-tetrahydrocannabinol (Δ^9^-THC) and other cannabinoids present in cannabis (marijuana) have been shown to affect the normal inhibitory pathways that influence nociception in humans. The potential benefits of cannabinoids as an analgesic are likely greatest in hyperalgesic and inflammatory states, suggesting a role as a therapeutic agent for treating acute pain following injury. Dronabinol is a licensed form of Δ^9^-THC. The primary objective of this single center randomized controlled trial is to evaluate the efficacy of adjunctive dronabinol versus control (systemic analgesics only, no dronabinol) for reducing opioid consumption in adults with traumatic injury. Study inclusion is based on high baseline utilization of opioids ≥50 morphine equivalents (mg) within 24 h of admission for adults aged 18–65 years with traumatic injury. There is a 48-hour screening period followed by a 48-hour treatment period after randomization. A total of 122 patients will be randomized 1:1 across 2 study arms: adjunctive dronabinol versus control (standard of care using systemic analgesics, no adjunctive dronabinol). Patients randomized to the dronabinol arm should receive their first dose within 12 h of randomization, with a dose range of 5 mg up to 30 mg daily in divided doses, in addition to systemic analgesics as needed for pain. The primary efficacy endpoint is a change in opioid consumption (morphine equivalents), assessed post-randomization (48 h after randomization) minus pre-randomization (24 h prior to randomization). This is the first randomized trial to investigate whether adjunctive dronabinol is effective in reducing opioid consumption in acute pain management of traumatic injury. Trial Registration: ClinicalTrials.gov Identifier: NCT03928015.

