## Figures and Tables

**Figure 1 brainsci-10-00161-f001:**
[figure not shown]
Subject Disposition.

**Table 1 brainsci-10-00161-t001:** Oral morphine milligram equivalents (MME) conversion factors.

Opioid (mg, Except Where Noted)	Oral MME Conversion Factor ^1^
Buprenorphine	N/A
Codeine	0.15
Fentanyl, intravenous (mcg)	0.3
Hydrocodone	1
Hydromorphone	4
Meperidine	0.1
Methadone	3
Morphine, oral	1
Morphine, intravenous	3
Oxycodone	1.5
Tramadol	0.1

^1^ Formula: Strength per Unit X (Number of Units/Days Supply) X MME conversion factor = MME/Day.

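### The primary endpoint sets a 48 h post-randomization period against a 24 h baseline total, in mg, without a common time base, and so does not fit the reductions used for sizing.

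*Protocol article*

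**What the plan says.** The Abstract and section 2.7 define the primary endpoint in the same way. In 2.7 the change "will be assessed as: post-randomization (48 h after randomization) minus pre-randomization (24 h prior to randomization"; in the Abstract it is "assessed post-randomization (48 h after randomization) minus pre-randomization (24 h prior to randomization".

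The baseline is an amount over a window: at screening (section 2.3) staff are to "record 24-hour total morphine equivalents". The post-randomization figure of 48 h coincides with "a 48-hour treatment window" in section 2.1. Section 2.7 keeps the difference in mg: "The change in morphine equivalents (mg) will be analyzed with an analysis of covariance (ANCOVA) model to examine the effect of treatment arm".

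Two other places bear on how the 48 h is meant. Section 2.6 says "The clinical effects of treatment arm on morphine equivalents will be evaluated at 48 h after randomization". The Table 1 footnote gives a conversion that ends in a daily rate: "Strength per Unit X (Number of Units/Days Supply) X MME conversion factor = MME/Day".

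Section 2.8 reads: "The sample size is based on a 38% reduction in morphine equivalents with adjunctive dronabinol vs. an 8% reduction in morphine equivalents" for the control arm, with a pooled SD of 58 (no unit), 122 patients and 80% power.

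**The concern.** The post-randomization period is twice as long as the baseline period, and neither 2.6 nor 2.7 halves it, expresses it per day or selects a 24 h part of it. A consumption total grows with the length of the window. A plain difference of the two totals therefore mixes a change in use with a change in observation time.

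At stake is what the primary result means. The objective is a reduction in opioid use, and the sample size is stated in reductions. Literal scoring could show a rise in both arms although daily use had fallen in both, and a difference in mg about twice the daily effect. If another reading is intended, the same chart gives a different number. Section 2.4 leaves the statisticians unblinded and section 2.9 applies an interim stopping rule to this endpoint, so the choice should not be made once results by arm can be seen.

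**Working it through.** **1. The plan's own figure.** Inputs from section 2.8: 38% and 8% (difference 30 points), SD 58, 61 per arm, two-sided alpha 0.05, normal approximation.
- z = 30 / (58 × √(2/61)) = 2.857. Power = Φ(2.857 − 1.960) = 81.5%, in line with the stated 80%.
- This treats 58 as percentage points, like 38 and 8. If 58 were mg and were paired with the 70 mg difference of the preliminary study (Introduction), n per arm = 2 × (1.960 + 0.842)² × 58² / 70² = 10.8, or 22 patients in total rather than 122. The sizing therefore appears to be on a percentage scale, while the endpoint is in mg.

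**2. The literal score.** Let B be baseline use per 24 h and r the proportional change in daily use. The 48 h total is 2B(1 + r), so the score is 2B(1 + r) − B = B(1 + 2r).

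| Change in daily use | 48 h total minus 24 h total | Common 24 h base |
|---|---|---|
| none (r = 0) | +100% of B | 0% |
| −8% (control) | +84% | −8% |
| −38% (dronabinol) | +24% | −38% |
| −50% | 0% | −50% |

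The between-arm difference is 24 − 84 = −60 points, against −38 − (−8) = −30 on a common base.

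**3. In mg.** The document gives no mean baseline, so these values are assumed; 50 mg is the inclusion threshold.

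| Baseline, mg/24 h | Dronabinol | Control | Difference | Difference per 24 h |
|---|---|---|---|---|
| 50 | +12 | +42 | −30 | −15 |
| 100 | +24 | +84 | −60 | −30 |
| 200 | +48 | +168 | −120 | −60 |

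**4. Power.**
- As a percentage of each patient's own baseline, the literal score is 100 + 2x, where x is the percentage change on the common base. Difference and SD both double (60 and 116), and power stays at 81.5%.
- In mg it depends on the pre/post correlation ρ, which the document does not give. Assume a mean baseline of 100 mg, equal SDs s for daily use before and after, and an SD of 58 for the daily change. Then s = 58 / √(2 − 2ρ), and the literal score has SD s × √(5 − 4ρ).
  - ρ = 0: SD 91.7, power 95%.
  - ρ = 0.5: SD 100.5, power 91%.
  - ρ = 0.7: SD 111.1, power 85%.
  - ρ = 0.75: SD 116, power 81.5%, the same as on the common base.
  - ρ = 0.9: SD 153.5, power 58%.
- If baseline use is a linear covariate in the ANCOVA, it absorbs the subtracted B. Both versions then give the same test, with an estimate that differs by a factor of two. Section 2.7 names age, gender and injury severity score; baseline use could enter only through the p < 0.15 rule for imbalanced characteristics.

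**5. The readings do not measure the same thing.** The first dose may come up to 12 h after randomization (section 2.5). A 0-48 h window can thus hold 12/48 = 25% of time before dosing, while a 24-48 h window holds none if that limit is kept.

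**The case against.** The best defence is that a comparable-window comparison was intended and badly worded. No sentence calls the outcome a 48-hour total; only the baseline is called a total. Evaluation at 48 h could mean the most recent 24 h. The Table 1 formula yields a daily rate, which would equalise the windows, and the percentage reductions in 2.8 make sense only on such a basis. This stands as far as intent goes. It does not settle the definition: the footnote is a dispensing formula based on days supplied, 2.7 does not invoke it, and 2.7 states the change in mg.

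A reader might go further in four ways that the document does not support.
- **That the trial will certainly report a reduction as a rise.** This takes the cumulative reading as settled. It is the most natural reading but not the only one.
- **That the treatment comparison is reversed or invalid.** The objective is dronabinol versus control, tested as an arm effect; section 2.7 describes no within-arm test. Both arms carry the same mismatch, so the contrast keeps its sign and its null value. Under randomization its expectation is the between-arm difference in 48 h use, a legitimate quantity.
- **That the change must stay positively related to baseline.** If b is the slope of post on pre daily use, the literal score has slope 2b − 1, which is zero at b = 0.5. The document gives no b.
- **That the result could not be compared with the preliminary study's −79 and −9 mg.** The article does not state that study's windows for these figures, so this cannot be judged either way.

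**Conclusion.** The point holds in a limited form. The definition, as worded in the Abstract and 2.7, pairs periods of unequal length without a common time base, and its literal reading conflicts with section 2.8. On that reading the planned 38% and 8% reductions score +24% and +84% of baseline, a negative score needs a fall of more than 50%, and the between-arm difference is 60 points rather than 30.

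These figures assume that the 2.8 percentages refer to equal-length or per-day amounts, which the word reduction implies but the document does not state. The damage is to the within-arm change, the size of the effect in mg, and agreement with the sizing. Direction and null hypothesis are intact. Power is little affected, on the assumptions shown, unless pre/post correlation exceeds 0.75 and baseline use stays out of the model.

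**What to change.** Before any unblinded or interim look, write one definition with one window and one time base, and use it in the Abstract, 2.6 and 2.7. One option is (total MME in hours 0-48 after randomization / 2) minus MME in the 24 h before randomization, in mg per 24 h. Another equal-length window, such as a stated 24 h period after randomization, would also serve, provided that it is named.

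In 2.8, state the unit and time base of the 38%, the 8% and the SD of 58, and confirm that they match the endpoint. It would also help to say in Table 1 how administered doses are summed over the window, since a days-supply formula does not describe inpatient dosing.

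The cost is wording in the protocol and analysis plan and one line of programming. No new data or extra patients are needed. With half the 0-48 h total, the planned effects return to −38% and −8%, the difference is 30 points, and power at 61 per arm is 81.5% on the 2.8 inputs.
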